**Ethics**

The study reviewed and approved by the Haramaya University, College of Health Science ethical review committee. The purpose of the study will be explained to the participants. Written consent will be obtained from the caregivers of children. They will be given enough time to decide to participate or to say no. If they do not wish to answer any questions during the data collection, they can say no and the interviewer will move on to the next questions. They will be informed to ask questions at any time. Oral consent will be secured from the partner of the caregiver, community leaders and local administrators. The researcher will arrange the provision of ORS to mothers/caregivers whose children are with diarrhoea at the time of study and advise to attend the nearby health institution.

**Risks and discomforts**

There are no known risks related to the study.

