**Enrolment and randomization**

We will use cluster level randomization to avoid ethical concerns and minimize the potential transfer of the intervention between the two groups. Ethiopian population census enumeration area map will be used to identify the clusters. There are 64 clusters (enumeration area) in study site. We will randomly select 36 clusters to participate in the study. Cluster selection will be done by central statistics authority using simple random sampling. Households in the selected clusters with at least one child under the age of five year will be identified by census. This is because we are expecting higher prevalence and incidence of diarrhea and the effect of the intervention would be higher among this group. Twenty four children will be selected randomly from the each cluster for follow up. Assigning of the clusters in to the intervention and control group will done by independent person using random sampling technique. Field workers will approach selected households in each cluster for baseline survey.

64 clusters

Randomly selected

36 cluster

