**Follow up Follow up**

6921 person week observation

Intention to treat analysis

6921 person week observation

Intention to treat analysis

**An**

**Baseline survey:** we will collect basic information including demographic and socioeconomic information, water sources and water handling practices, access and water quality, housing conditions, and pre-intervention diarrhea rates.

**Interventions:** The intervention for this study will be 1.25% Sodium hypochlorite solution locally branded as “watergauard”. The intervention household will receive the hypochlorite disinfectant for household water treatment while the control groups will continue their usual practice. Both the intervention and control households use Jerricans for water collection and storage. Local women will be selected for the distribution of the intervention (sodium hypochlorite). They will be trained on how to use sodium hypochlorite for household water treatment and explain to the intervention households how to treat water. The intervention will be distributed for 16 weeks.

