**Diarrhoea monitoring**

The survey instrument will be pre-tested and validated in the nearby villages. Field workers will use a validated questionnaire to record the occurrence of diarrhea in children under the age of five years, water treatment practices and residual chlorine in the selected households on weekly bases. A female caregiver will provide the information.

**Anthropometric measurement:** The secondary outcome for this study is weight gain. All fieldworkers will be trained on anthropometric measurement techniques over two days of training, and they will collect measurements in teams of two. Fieldworkers will measure the weight of children using digital scales. These scales will be calibrated every day before starting the data collection. Anthropometric measurement will be taken at the baseline and the end of the

Study.

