**Laboratory measurements**

Residual free chlorine concentration will be measured from the samples of stored household water once a week and on unannounced visits by using the residual chlorine test kit(Wagetech 225 comparator colour disc**) .**Water samples will be collected from randomly selected 50% of the households water storage containers from both the intervention and control groups at the baseline and end of the study. The samples will be collected with sterile technique in 150 ml sterile plastic vessels containing sodium thiosulfate to neutralise any free chlorine in the water samples. Environmental health science graduates will collect samples and transport with icepacks to the Haramaya University bacteriology laboratory for processing within six hours of collection for analysis**.** Most probable number (MPN) will be used for the analysis of the sample and MPN table to quantify Escherichia coli which are regarded as the most reliable indicator of fecal contamination (wright 2004)

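### The risk section says there are no known risks, but a hypochlorite solution is kept for 16 weeks in homes with under-fives, and the protocol states no recording of, or response to, accidental exposure

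*Protocol*

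**What the plan says.** The Risks and discomforts section of the protocol is one sentence: "There are no known risks related to the study". It carries no qualification and covers the study as a whole.

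Other sections describe what is supplied, to whom, and what is recorded:

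- **Product and duration (Interventions).** "The intervention for this study will be 1.25% Sodium hypochlorite solution locally branded as" a named household product, and "The intervention will be distributed for 16 weeks".
- **Recipients (Enrolment and randomization).** "Households in the selected clusters with at least one child under the age of five year will be identified by census".
- **Instruction (Interventions).** Of the local women who distribute the product: "They will be trained on how to use sodium hypochlorite for household water treatment and explain to the intervention households how to treat water".
- **Weekly record (Diarrhoea monitoring).** Field workers record diarrhoea, "water treatment practices and residual chlorine in the selected households on weekly bases".
- **Clinical response (Ethics).** The only one stated is for diarrhoea. Oral rehydration salts are arranged for caregivers "whose children are with diarrhoea at the time of study and advise to attend the nearby health institution".

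The Ethics section also records ethics committee approval and written consent from caregivers.

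**The concern.** A disinfectant solution kept at home within reach of small children can be swallowed by accident or splashed on skin or in eyes. A protocol may fairly call that risk low. Saying that no risk is known is a different claim, and it does not fit what the trial places in these homes.

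Two omissions follow from that sentence. The weekly record, as the protocol describes it, has no item for such an event. The field worker who hears of one has no stated step to take. At stake is the safety of participating children, and the trial's ability to say at the end whether any product accidents happened. The primary and secondary analyses are untouched.

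**Working it through.** The risk section states no figure and no formula applies, so the check is to set the sections side by side.

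1. **Is there a hazard to disclose?** Interventions puts 1.25% sodium hypochlorite in intervention households for 16 weeks. Enrolment and randomization identifies study households by the presence of a child under five. Together these mean a disinfectant is stored in homes with young children. That accidental swallowing or contact is foreseeable is general reasoning. The protocol does not say so and gives no rate.

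2. **Does the risk section allow for it?** No. Its single sentence makes no exception for storing or handling the product. The Benefits section that follows credits the intervention with possible gains for the whole family, so the product is counted for benefit and not for risk.

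3. **Would an event be recorded?** Diarrhoea monitoring names three topics for the weekly record: diarrhoea, water treatment practices and residual chlorine. None is an accidental exposure.

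4. **Would households be warned?** Interventions describes the distributors' training, and what they pass on, as how to use the product and treat water. Safe storage and accidental contact are not mentioned.

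5. **Would anyone act?** Ethics gives a response for a child with diarrhoea: rehydration salts and advice to attend a local health facility. No section gives one for exposure to the product. The protocol does state a clinical response where it foresees a need, and the referral part of it could serve here unchanged.

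On all five steps the protocol text is silent, or in step 2 says the opposite. The number of homes holding the product is not used as a measure of size. It would depend on assumptions about who is supplied and how many selected children share a home, and it would say nothing about how often exposure occurs.

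**The case against.** The strongest reply has three parts.

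**The hazard is not in the documents.** No section says that the solution is harmful, and the risk sentence could be read as meaning no known risk beyond using a locally branded product as directed. It is true that the inaccuracy rests on ordinary judgement and not on two sections contradicting each other. But that a disinfectant can be swallowed or splashed is common knowledge, and the sentence contains no limit to directed use.

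**The rest may be covered elsewhere.** Diarrhoea monitoring lists topics, not questionnaire items. Training in how to use the product could include safe handling. Consent pages, where risks are usually described, are not available. This stands as a limit: a reader might infer that caregivers were never warned or that accidents were never asked about, and the documents do not support that. The point concerns only what the protocol states. A warning in other papers would not make the risk sentence accurate; it would conflict with it.

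**A fix could do damage.** A reader might also infer that the protocol needs an action for high chlorine readings, since Laboratory measurements says "Residual free chlorine concentration will be measured from the samples of stored household water once a week and on unannounced visits". The documents do not support that either. They give no upper limit, state no safety purpose for the readings and do not suggest that overdosing is expected. Sending a child to a clinic does not fit a reading taken on stored water. The section on limitations and strengths also keeps those who deliver the intervention apart from those who collect data, as the safeguard against bias in an unblinded trial. Data collectors acting on readings would weaken that separation. This objection succeeds, and no such action is asked for.

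**Conclusion.** The point holds in a limited form. The risk sentence is inaccurate for a trial that keeps a hypochlorite solution in homes with young children, and the protocol text states neither recording of nor response to accidental swallowing or eye or skin contact.

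Its size cannot be expressed as a number. The documents give no exposure or harm rate, and the risk is taken here to be low. No estimate, test or sample size changes. It would go too far to infer that the trial is unsafe or that the ethics approval was unsound: nothing in the documents shows either.

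The conclusion assumes only that accidental contact with a stored disinfectant is foreseeable. The questionnaire, training material or consent pages may already fill part of the recording and warning gap. This is an optional but worthwhile improvement.

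**What to change.** Make three changes to the protocol.

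1. **Risks and discomforts.** Replace the sentence with a statement that storing and handling the product carries low but foreseeable risks of accidental swallowing and of eye or skin contact.
2. **Diarrhoea monitoring.** Add one question to the existing weekly visit, in both arms, on any accidental swallowing of, or eye or skin contact with, a water-treatment product since the last visit. Report the answers by arm. The general wording suits control households, which continue their usual practice.
3. **Ethics.** State that any reported exposure leads to referral to the same local health facility as already named for diarrhoea.

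No action on chlorine readings is needed. If the investigators want one, it should be re-instruction on dosing given by the distributors, so that data collectors stay out of delivering the intervention.

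The changes need no extra visits, staff or samples. The costs are a slightly longer interview and a less reassuring risk statement. Asking weekly about product accidents might also have a small prompting effect on use of the product, and so on acceptability, which is a secondary objective. The size of that effect is unknown.

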**Benefits**

The intervention may reduce the prevalence and incidence of diarrhoea and other water related diseases. Therefore, the family as a whole could directly benefited from the intervention. The benefit is expected to be more in under-five children where the prevalence of diarrhoea is high.

**Confidentiality**

We will not be sharing the information out side of the research team. The information that we collect from this research project will be kept confidential. Information collected from the research will be put away and no-one but the researchers will be able to see it. Any information will have a number on it instead of his /her name. It will not be shared with or given to anyone except the investigator or data clerk.

**Sharing of research findings**

At the end of the study, we will be sharing what we have learnt with the participants and with the community. We will do this by meeting first with the participants and then with the larger community. A written report will also be given to the participants whom they can share with their families. We will also publish the results in order that other interested people may learn from our research.

